## Abstract

**Introduction:**

Regulatory T cell (Treg) therapy has been demonstrated to facilitate long-term allograft survival in preclinical models of transplantation and may permit reduction of immunosuppression and its associated complications in the clinical setting. Phase 1 clinical trials have shown Treg therapy to be safe and feasible in clinical practice. Here we describe a protocol for the TWO study, a phase 2b randomised control trial of Treg therapy in living donor kidney transplant recipients that will confirm safety and explore efficacy of this novel treatment strategy.

**Methods and analysis:**

60 patients will be randomised on a 1:1 basis to Treg therapy (TR001) or standard clinical care (control). Patients in the TR001 arm will receive an infusion of autologous polyclonal ex vivo expanded Tregs 5 days after transplantation instead of standard monoclonal antibody induction. Maintenance immunosuppression will be reduced over the course of the post-transplant period to low-dose tacrolimus monotherapy. Control participants will receive a standard basiliximab-based immunosuppression regimen with long-term tacrolimus and mycophenolate mofetil immunosuppression. The primary endpoint is biopsy proven acute rejection over 18 months; secondary endpoints include immunosuppression burden, chronic graft dysfunction and drug-related complications.

**Ethics and dissemination:**

Ethical approval has been provided by the National Health Service Health Research Authority South Central—Oxford A Research Ethics Committee (reference 18/SC/0054). The study also received authorisation from the UK Medicines and Healthcare products Regulatory Agency and is being run in accordance with the principles of Good Clinical Practice, in collaboration with the registered trials unit Oxford Clinical Trials Research Unit. Results from the TWO study will be published in peer-reviewed scientific/medical journals and presented at scientific/clinical symposia and congresses.

**Trial registration number:**

ISRCTN: 11038572; Pre-results.

Strengths and limitations of this studyRandomisation will provide a contemporary control group to compare outcomes following regulatory T cell therapy and immunosuppression minimisation.Absence of an induction agent, day 5 regulatory T cell infusion and protocol defined immunosuppression reduction to low dose tacrolimus monotherapy in the TR001 arm represents a significant reduction in pharmaceutical immunosuppression burden compared with standard care.Comprehensive clinical and immune monitoring planned over an 18-month follow-up will permit assessment of clinical safety and efficacy as well as exploration of markers of immune activation and tolerance.This study may be limited through being an open-label single-centre trial.As a phase 2b trial with small participant numbers in each arm this study is not powered to provide definitive proof of efficacy.

## Introduction

Kidney transplantation is the gold standard treatment for patients with end-stage kidney disease and is associated with excellent short-term outcomes with graft survival of greater than 95% for living donor transplant recipients at 1 year.^1^ However, there remains significant scope for improvement in long-term outcomes with progressive reduction in graft survival over time.^1^ Furthermore, outcomes are limited by the complications of immunosuppression such as life-threatening infection, increased cardiovascular disease risk and malignancy.^2–5^ Novel treatments such as regulatory T cell (Treg) therapy may improve long-term patient and graft outcomes both by reducing immune mediated graft dysfunction and facilitating reduction of immunosuppression to minimise the associated side effects.^6–8^

Tregs are typically defined by expression of the cell surface markers being CD4^+^CD25^+^ and their constitutive expression of the master transcription factor FOXP3. Extensive preclinical models have demonstrated their potency at suppressing rejection responses resulting in long-term allograft survival in the absence of pharmaceutical immunosuppression.^9–11^ The first steps in translation of Treg therapy into the clinical setting of organ transplantation were taken by Todo *et al* who infused a Treg enriched cell product (less than 15% Treg) into liver transplant recipients.^12^ Seven of 10 patients were able to completely withdraw immunosuppression although 3 patients experienced rejection episodes. The low purity of Tregs in the infused cell product and incidence of spontaneous tolerance in liver transplant recipients makes interpretation of these results uncertain. In kidney transplantation, we have recently demonstrated successful infusion of autologous polyclonal Tregs into 12 patients recruited as part of the ONE study consortium.^13 14^ This phase 1 trial used dose escalation from 3×10^6^ to 10×10^6^ Tregs/kg bodyweight infused at day 5 post transplantation. Participants did not receive any monoclonal antibody induction therapy and were initially maintained on prednisolone, mycophenolate mofetil and tacrolimus. Immunosuppression was weaned over the course of the first year and 4 of 12 patients were ultimately successfully reduced to tacrolimus monotherapy. Four-year follow-up demonstrated no episodes of rejection compared with a 21.1% rejection rate in a retrospective control cohort receiving standard care. Furthermore, there was a suggestion of reduced incidence of opportunistic cytomegalovirus (CMV) and BKV infections.^13^ Our ONE study colleagues in Berlin infused 11 patients with autologous polyclonal Tregs in a dose escalation manner at day 7 post transplant.^15^ Eight patients were weaned successfully to tacrolimus monotherapy. Three of 11 patients experienced biopsy proven acute rejection, a rate similar to that seen in patients undergoing standard care.^15^ These studies have demonstrated initial safety and feasibility of Treg therapy and provide justification for continuation into phase 2 trials.^14^

The TWO study will build on our work performed as part of the ONE study consortium^14^ to provide further evidence of safety and to explore efficacy of Treg therapy to facilitate immunosuppression reduction in living donor kidney transplant recipients.

The TWO study was originally conceived as a phase 2b randomised (1:1) control trial of Treg therapy versus standard care in 68 living donor kidney transplant recipients. Patients in both arms received standard alemtuzumab induction at the point of transplant to facilitate lymphodepletion with a view to optimising the environment into which Treg were later infused in favour of tolerance induction.^16^ Immunosuppression in the Treg arm was minimised to tacrolimus monotherapy in advance of cell infusion at 6 months post transplant and compared with ongoing standard maintenance immunosuppression with tacrolimus and mycophenolate mofetil. Target tacrolimus levels were reduced in the cell therapy arm to 4–6 ng/mL from week 40 post transplant. The primary outcome was incidence of biopsy proven acute rejection between 6 and 18 months post transplant.

Nine patients were recruited to this protocol and seven transplanted prior to the emergence of the COVID-19 pandemic. Due to concerns related to an increased risk of severe COVID-19 in the setting of alemtuzumab lymphodepletion, the trial protocol was modified to one using basiliximab-based induction immunosuppression. Basiliximab is a widely used induction immunosuppressive agent that binds to and blocks CD25, the alpha chain of the interleukin (IL)-2 receptor, resulting in T cell suppression. Seven patients treated under the original protocol with alemtuzumab induction will be reported as a cohort demonstrating our experience of Treg administration in this context. The current protocol comparing Treg therapy to basiliximab-based standard immunosuppression will recruit 60 participants, form the basis of the TWO study and is reported in detail here.

## Methods and analysis

### Patient and public involvement

Patients were involved in the design and conduct of the TWO study. During development the proposed study was presented and discussed with a patient focus group to ensure that it addressed a relevant need to the transplant patient community. Methodology was discussed to ensure acceptability and address any concerns. A transplant recipient has joined the independent trial steering committee (TSC) bringing an invaluable patient perspective to discussions. Once the trial has been published, participants will be informed of the outcomes directly and results will be distributed to relevant patient groups.

### Study design

In this parallel group, phase IIb trial, 60 eligible living donor kidney transplant recipients will be recruited from that undergoing kidney transplantation at a single academic hospital (Oxford Transplant Centre, Churchill Hospital, Oxford, UK) and randomised on a 1:1 basis to receive a standard basiliximab-based immunosuppressive regimen (control arm) or Treg infusion associated with immunosuppression reduction (TR001 arm) (figure 1).

**Figure 1 F1:**
[figure not shown]
Diagrammatic representation of the immunosuppressive regimen used in The TWO study.

Participants will be approached and enrolled by the clinical principal investigator (PI) or deputy following approval of listing for living donor kidney transplantation by the clinical multidisciplinary team meeting. Randomisation is computer generated and performed by minimisation, with stratification for ethnicity and Human Leukocyte Antigen - DR (HLA-DR) mismatch. Treatment allocation will be open-label as pre-transplant venesection of blood for Treg manufacture in those allocated to the TR001 arm is required and it is not ethically appropriate to perform venesection in control patients prior to major surgery. Accordingly, outcome assessors and statisticians are not blinded.

With a relatively small patient sample size, the emergence of significant numbers of patient discontinuation in the trial may obscure the true outcome of this research. Discontinued participants may be replaced by the recruitment of additional patients. The decision to replace individual patients will ultimately be made by the clinical PI on the basis that some unanticipated factor may influence the clinical outcome in terms of the primary endpoint.

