### Primary outcome

The primary outcome is incidence of biopsy-confirmed acute rejection (BCAR) in the 18 months post transplantation. A diagnosis of BCAR can be made based on protocol driven or clinically indicated ‘for cause’ biopsies. ‘For cause’ biopsies may be performed during follow-up at the discretion of the responsible clinician taking into account the full clinical picture and are typically triggered by an unexplained rise in serum creatinine as per standard National Health Service (NHS) practice. Whenever rejection is suspected, a for-cause graft biopsy will always be offered and performed with the patient’s permission. The results of for-cause biopsies will be available to the trial investigators and the outcome will be documented in the electronic database.

All biopsies performed will be reviewed and reported by the study pathologist using the internationally accepted Banff criteria. Whenever a biopsy is reported as suspicious for rejection or borderline changes, responsibility for a diagnosis of rejection lies with the treating physician.

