Assays will be performed to investigate whether cell therapy shifts kidney transplant recipients towards a more tolerance-prone phenotype or away from a rejection-prone phenotype. Gene expression of a defined set of tolerance-associated genes in whole blood will be profiled by quantitative PCR. Leucocyte subset profiling will be performed by flow cytometry to quantify immune cell subpopulations in patient peripheral blood. Donor-reactive T cell frequencies will be measured following co-culture of recipient T cells with stored donor derived antigen presenting cells using a CD154/137 assay. This assay will be performed before and after transplantation to enable an estimation of the pre-transplant frequency of donor-reactive T cells, and detection of post-transplant sensitisation against donor antigen. Treg frequencies in patient blood will be measured by epigenetic analysis of the Treg-specific demethylated region of the FOXP3 gene. Finally, cytokine and metabolic profiling will be performed assessing inflammatory and regulatory cytokines as well as low-molecular-weight metabolites to provide a picture of the dynamic changes that may take place in the immune response after cellular therapy and immunosuppression modification.

Histopathological samples will be taken at 5 months (protocol biopsy) in kidney transplant recipients randomised to the TR001 arm. This biopsy will confirm the ongoing safety of Treg therapy and ensure no evidence of subclinical rejection. A 9-month protocol biopsy will be performed in all participants including the control arm to allow a histological comparison of the impact of Treg therapy.

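### The reason given for leaving outcome assessors unblinded does not apply to the pathologist who grades every biopsy, so an inexpensive protection of the primary endpoint is given up

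*Protocol article*

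**What the plan says.** The protocol article, Study design (text under Figure 1), gives one argument for the open-label design. Patients in the cell therapy arm must give blood before the operation so that their product can be made. Of a matching procedure in the other arm, the article says "it is not ethically appropriate to perform venesection in control patients prior to major surgery". The next sentence presents the masking of readers and analysts as a consequence: "Accordingly, outcome assessors and statisticians are not blinded".

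The Primary outcome section defines the endpoint: "The primary outcome is incidence of biopsy-confirmed acute rejection (BCAR) in the 18 months post transplantation". It names one reader: "All biopsies performed will be reviewed and reported by the study pathologist using the internationally accepted Banff criteria". No coded reading or independent second reading is described. Two further steps belong to the clinic. On unclear histology, "Whenever a biopsy is reported as suspicious for rejection or borderline changes, responsibility for a diagnosis of rejection lies with the treating physician". On when to sample outside the schedule, for-cause "biopsies may be performed during follow-up at the discretion of the responsible clinician".

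The Immune monitoring section adds a biopsy in one arm only: "Histopathological samples will be taken at 5 months (protocol biopsy) in kidney transplant recipients randomised to the TR001 arm". It also places a 9-month protocol biopsy in both arms. The strengths and limitations list names the open-label, single-centre design as a possible limitation but says nothing about masking of assessors.

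**The concern.** The conclusion does not follow from the reason. Without sham venesection, patients and the staff who treat them will know the arm. A pathologist looking at tissue need not. The article therefore treats an avoidable source of detection bias as unavoidable. Because it states the non-blinding outright and gives a reason, this is not a detail left to a fuller document.

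The pathologist's reading feeds the primary event, and by the Secondary outcomes section also the histological severity of rejection and the Banff staging of chronic damage. It also determines whether a biopsy is reported as rejection, borderline or neither, and so which biopsies reach the treating physician for a decision. Banff criteria limit the reader's discretion without removing it. The comparison is meant to indicate whether a phase 3 trial is appropriate and to supply its sample-size inputs, so a biased rate would carry forward.

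**Working it through.** **Inputs.** 30 patients per arm (60 randomised 1:1, Abstract and Study design). Control rejection rate 12–20% over 18 months (Sample size calculation). 20% significance and 80% CIs (Data analysis plan); sidedness is not stated, so two-sided is assumed, with critical value 1.2816.

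**The plan's own figure.** The 80% Wilson interval at n = 30 has width 9.5% at 1/30 and 22.8% at 15/30. This reproduces the stated 10–23%; only 0/30 (5.2%) falls outside. Masking the reader changes none of this.

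**Who is affected by the stated reason.**

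| Person | Does venesection reveal the arm? | Is masking possible? |
|---|---|---|
| Patient | Yes | No, without sham venesection |
| Treating clinician | Yes | No |
| Study pathologist | Not from the tissue | Yes, with coded samples, except where timing reveals the arm |

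**Expected events.** 30 × 0.12 = 3.6; 30 × 0.16 = 4.8; 30 × 0.20 = 6.0. One biopsy that changes a patient's status moves an arm's rate by 1/30 = 3.3 points.

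**One reading near the threshold.** The statistic is z = (difference in proportions) / √[p̄(1 − p̄) × 2/30], with p̄ the pooled proportion.

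- 6/30 v 3/30: p̄ = 9/60 = 0.150; z = 0.100/0.0922 = 1.08; p = 0.28.
- 6/30 v 2/30: p̄ = 8/60 = 0.133; z = 0.133/0.0878 = 1.52; p = 0.13.

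One event fewer takes the result across the 20% level.

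**Reading bias, under assumption.** The documents give no misreading rate. Take equal true rates p, and suppose a fraction m of TR001 rejections is under-called, so that the TR001 arm shows p(1 − m). Summing over all pairs of Binomial(30) outcomes gives the chance of a significant result favouring TR001:

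| True rate | m = 0 | m = 5% | m = 10% | m = 20% |
|---|---|---|---|---|
| 12% | 10.6% | 12.0% | 13.5% | 17.1% |
| 16% | 10.8% | 12.4% | 14.2% | 18.5% |
| 20% | 10.8% | 12.8% | 15.0% | 20.2% |

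**The other direction.** If instead 5% or 10% of non-rejecting patients in one arm are over-called, the chance of any significant difference rises from 21–22% to 25–27% or 32–39%. A real difference can also be hidden. With assumed true rates of 16% v 30%, power is 0.53 without bias, 0.43 if 10% of rejections in the higher arm are missed, and 0.34 if 20% are missed.

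The article names the log-rank test for significance. The comparison of proportions used here is an approximation to it.

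**The case against.** **Purpose and disclosure.** The non-blinding is disclosed, the trial is said not to be powered for definitive proof of efficacy, and a single reader applying Banff criteria restrains variation. These points reduce the harm, and this part of the objection stands. They do not repair the reasoning or make masking of the reader harder.

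**The more subjective steps lie elsewhere.** The treating physician decides borderline or suspicious reports, and clinicians decide when to take a for-cause biopsy; both know the arm. The 22-week biopsy exists only in TR001, so its timing gives the arm away, and it is also an imbalance in detection that no blinding removes. This stands too: masking the pathologist is a partial remedy.

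**Size.** A reader might infer that unmasked reading could make a false positive about as likely as not. Removing two or three TR001 rejections in every hypothetical trial does give about 34% or 51% at a 16% rate. But against 3.6 to 6.0 expected events, two removals mean misreading 33–56% of that arm's rejections, and three mean 50–83%. Nothing in the document supports such rates.

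**Statistician and laboratory staff.** A reader might extend the point to both. The open modelling choices are matters commonly left to a statistical analysis plan that is not shown. The immune assays are described as experimental and without influence on care. Neither extension is well supported.

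**Conclusion.** The point holds in a limited form. The stated reason covers patients and treating staff but not the histology reader, so the reader's unmasked status is a choice without a valid reason. It rests on one strong inference: that the outcome assessors include the study pathologist, the only biopsy reader the article names.

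The sensitivity of the result to a single reading near the threshold is arithmetic. The amount of bias is not known. Under the assumed 5–20% under-calling, with equal true rates of 12–20% and a two-sided 20% level, the chance of a significant result favouring TR001 rises from about 11% to between 12% and 20%. Bias in the opposite direction is equally possible. The document does not show that readings will be biased, nor that masking would make the endpoint fully objective. The change is worth making because it is inexpensive and protects the primary endpoint.

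**What to change.** Replace the sentence on assessors and statisticians in Study design with:

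*Patients and treating clinicians are not blinded. The study pathologist grades biopsies under study number with arm and cell infusion status withheld, and records the trial Banff grade before any unblinded clinical discussion; the arm may be disclosed afterwards if care requires it.*

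Apply this to the 38-week (9-month) protocol biopsies, which are taken in both arms, and to for-cause biopsies. State that the 22-week biopsy is taken only in TR001 and cannot be reliably masked. State also that borderline decisions and the decision to take a for-cause biopsy remain with clinicians who know the arm. Coded arm labels for the statistician are optional.

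**Cost.** Some relabelling of request forms and samples, and an initial grade given without the arm. The same pathologist reads the same biopsies, so no extra reader or procedure is needed. Whether request forms for clinically driven biopsies can leave out the treatment history cannot be judged from the article, and the trial team should check this.

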### Inclusion and exclusion criteria

Inclusion and exclusion criteria for both kidney transplant recipient and donor are listed in box 1. Specific to transplantation, exclusion criteria originally included a calculated reaction frequency (cRF) of >40% and a history of previous transplant. These were subsequently amended to permit recipients with a cRF of <60% and to allow patients with a previous transplant to participate. ABO blood group incompatible transplants, the presence of a pre-transplant donor specific antibodies (DSA), or a history of desensitisation continue to meet exclusion criteria to ensure those transplants with the highest immunological risk are not included in this phase IIb study.

Box 1Inclusion and exclusion criteria for TWO study transplant recipients and donors
**Kidney recipient inclusion criteria**
A prospective kidney transplant recipient is eligible for enrolment into the study if all of the following inclusion criteria apply:Chronic renal insufficiency necessitating kidney transplantation and approved to receive a kidney allograft from a living donor.Willing and able to give informed consent for participation in the trial.Aged 18 years or above.In the investigator’s opinion, is able and willing to comply with all trial requirements.Able to commence the immunosuppressive regimen at the protocol-specified time point.Female participants of child bearing potential and male participants whose partner is of child bearing potential must be willing to ensure that they or their partner use highly effective contraception during the first 18 months post transplant (see section on contraception).Willing to allow his or her general practitioner and consultant, if appropriate, to be notified of participation in the trial.
**Kidney recipient exclusion criteria**
The participant may not enter the trial if ANY of the following apply:Patient has previously received any tissue or organ transplant.*Known contraindication to the protocol-specified treatments or medications.ABO blood group incompatible with donor.Calculated reaction frequency (cRF) of >60%† within 6 months prior to transplant.Previous treatment with any desensitisation procedure (with or without IVIg).Concomitant malignancy or history of malignancy within 5 years prior to planned study entry (excluding successfully treated non-metastatic basal or squamous cell carcinomas of the skin).Serologically positive for anti-HIV-1/2 Ab, HbsAg, anti-HBcAb, anti-HCV Ab, anti-HTLV-1/2 Ab or syphilis (treponema palladium).Significant liver disease, defined as persistently elevated Alanine Aminotransferease levels >3 × upper limit of normal range.Any other significant disease or disorder which, in the opinion of the investigator, may either put the participants at risk because of participation in the trial, or may influence the result of the trial, or the participant’s ability to participate in the trial.Participation in another clinical trial during the study or within 28 days prior to planned study entry.Female participant who is pregnant, lactating or planning pregnancy during the course of the trial.Psychological, familial, sociological or geographical factors potentially hampering compliance with the study protocol and follow-up visit schedule.Any form of substance abuse, psychiatric disorder or other condition.
